**2.8.2 Secondary outcome**

The secondary outcomes of this study encompass two domains: knowledge of breast cancer and breast self-examination (BSE), and beliefs related to breast cancer and BSE.

**Knowledge of Breast Cancer and BSE:** The study will assess participants' knowledge through a comprehensive self-report questionnaire. These items will cover various aspects including breast cancer risk factors, signs and symptoms, breast health awareness including BSE practices, and breast cancer screening techniques. Participants' understanding of these critical areas will be evaluated to gauge their baseline knowledge and any improvements post-intervention.

**Beliefs about Breast Cancer and BSE:** Beliefs related to breast cancer and BSE will be measured using the modified Urdu version of the Champions Health Belief Model Scale (CHBMS). This scale will be modified, translated and validated by the researchers for this study. These subscales include perceptions of the severity and seriousness of breast cancer, perceived benefits and barriers of performing BSE, confidence levels in performing BSE, and motivation towards adopting BSE practices. By using this scale, the study aims to capture participants' attitudes and beliefs regarding breast cancer prevention and early detection through self-examination.

These secondary outcomes are crucial in understanding how participants' knowledge and beliefs influence their behaviors related to breast cancer screening practices, thereby informing the effectiveness of the educational intervention designed for this study.

## 2.9 Study instrument

A self-administered questionnaire will be used, the Questionnaire includes four sections:

**Section I** comprises socioeconomic characteristics (age, marital status, teaching experience, religion, family income, education level, native language, area of residence, presence of health personnel in immediate family, personal history of benign diseases, family history of breast cancer).

**Section II**: It consists of questions based on,

- Risk factors of breast cancer
- Symptoms of breast cancer

- BCS methods
- BSE

Responses will be measured by utilizing the nominal scale of “True”, “False” and “I do not know”. Respondents will score one point for every correct answer and will score zero points for uncertain or wrong response. The maximum knowledge considered will be 36and the minimum score will be 0. Scores will later be calculated for analysis; higher scores will be associated with greater knowledge.

**Section III: Health Belief Model Scales**

The CHBMS Champion (1993) and Champion (1999) will be used after getting permission from authors, in the current study, for measuring beliefs related to BC. The CHBM scale based on 6 self-reported measured scales are perceived susceptibility to breast cancer (5 items), perceived severity of breast cancer (7 items), perceived benefits of BSE (6 items), perceived barriers for breast self-examination (6 items), confidence in one’s ability to perform Breast self-examination (11 items), health motivation (7 items),., All scale items will be measured with a 5 point Likert scale with the coding mentioned below.

- Strongly disagree One point
- Disagree Two points.
- Neutral Three points
- Agree Four points.
- Strongly agree Five points

Then scores will be summed up for analysis. Higher scores will represent greater perception linked with that construct (Champion, 1995). All HBM scales are associated positively with breast cancer screening behaviors, excluding the barrier scale, which is linked negatively. Researchers used Bloom's cut-off point to categorize the total beliefs scores into three categories:(Abdullahi et al., 2016; Yimer et al., 2014).

- **Negative attitude:** (scores representing 0-49%)
- **Neutral attitude:** (scores representing 50-79%)
- **Positive attitude:** (scores representing 80-100%)

**Section IV: Breast self-examination practice and frequency**

BSE, practice, and frequency of performing BSE test will be measured by utilizing a self-reported instrument.

**Translation of original CHMBS into Urdu language:**

To translate the CHBMS into Urdu for use among Pakistani females, will be started by forming a specialized translation team comprising bilingual experts proficient in both English and Urdu. This team will include linguists with expertise in medical terminology, public health professionals familiar with the CHBMS, and native Urdu speakers to ensure the translation's cultural relevance and accuracy. Initially, two independent translators will translate the CHBMS from English to Urdu, following guidelines to maintain consistency in terms and concepts. These translations will then be reviewed by the team to address any discrepancies.

Next, is the reconciliation and harmonization of the translations into a single coherent version. A committee, including the initial translators and additional experts, will review and resolve any differences to ensure the Urdu version accurately reflects the original content and is culturally appropriate for Pakistani females. Following this, the Urdu version will undergo back-translation, where two independent translators, not involved in the initial translation, will translate the Urdu version back into English. This process will help identify inconsistencies or errors, which will be addressed through further refinement of the Urdu translation.

To ensure the translation's comprehensibility and cultural relevance, the Urdu version will be pre-tested with a small group of Pakistani females. Cognitive interviews will be conducted to gather feedback on the clarity and cultural appropriateness of the translation, and adjustments will be made based on this feedback. After final revisions, Urdu CHBMS will undergo a final review by the translation team and additional experts to ensure accuracy and appropriateness.

## 2.10 Quality control of the questionnaire

**Validity**

**Face Validity**

To ensure the reliability and effectiveness of our questionnaire, face validity will be assessed by five experts from University Putra Malaysia. Face validity refers to the extent to which a test or questionnaire appears to measure what it is supposed to measure, based on subjective judgment. This type of validity is important as it will help establish the credibility of the instrument in the eyes of respondents and stakeholders. The experts will review the questionnaire for clarity, relevance, and comprehensiveness, providing critical feedback on the appropriateness of the questions and their alignment with the study objectives.

In addition to expert validation, feedback from a group of five participants will also be collected. This step will be crucial for understanding how the target population perceives the questionnaire. The participants' feedback will help identify any ambiguities or difficulties in understanding the questions, ensuring that the language and content are appropriate and comprehensible to the intended audience. This dual approach of involving both experts and participants in the validation process will help enhance the questionnaire's face validity, making it a more reliable tool for measuring knowledge, beliefs, and practices related to breast self-examination. By addressing potential issues identified during this phase, we will improve the questionnaire's overall quality and ensure that it will effectively capture the necessary data for our study.

**Content validity**

To ensure the robustness and relevance of our questionnaire, content validity will be rigorously assessed by a panel of experts from University Putra Malaysia (UPM) and Pakistan. Content validity involves evaluating whether the instrument will comprehensively cover the construct it aims to measure. This process will help ensure that all relevant aspects of the subject are included, and the items accurately reflect the intended content domain.

Each item in the questionnaire will be evaluated for content validity using the Content Validity Index (CVI). CVI is a widely used statistical measure that quantifies the degree of agreement among experts regarding the relevance of individual items. For our study, the Item-level Content Validity Index (I-CVI) will be calculated for each question. The I-CVI represents the proportion of experts who rate the item as either relevant or very relevant.

Items with an I-CVI above a predetermined threshold, such as 0.78 or 0.80, will be considered to have good content validity. This threshold will ensure a high level of agreement among the experts regarding the relevance and appropriateness of the items. Items that do not meet this criterion will be reviewed and revised based on the experts' feedback or removed from the questionnaire to maintain the overall quality and relevance of the instrument.

This thorough process of assessing both face and content validity will help ensure that our questionnaire is not only clear and understandable to participants but also comprehensive and relevant to the study's objectives. By incorporating expert feedback and adhering to rigorous validation criteria, we aim to create a reliable tool capable of accurately measuring knowledge, beliefs, and practices related to breast self-examination among college teachers in Hyderabad, Pakistan.

**Reliability**

The reliability of our measurement instrument will be assured through various strategies tailored to the study's context and informed by previous research. Specifically, for items designed to measure attitudes, we will assess reliability using Cronbach's alpha, with a threshold set at 0.70 or higher to ensure internal consistency. Corrections will be made based on test outcomes to enhance reliability. Furthermore, employing consistent data collectors who will assess research participants both at baseline and during follow-up will add an extra layer of assurance regarding the instrument's reliability.

The questionnaire to be utilized in this cluster randomized controlled trial (cRCT) will be a validated and reliable tool, rigorously tested for validity and reliability by the study researchers before its deployment.

## 2.11 Data collection

With the help of college coordinators, small meeting groups will be arranged in colleges. All the selected participants will be informed about the purpose and procedures of breast cancer awareness and BSE practices educational intervention trial by the researcher as well as the selection criteria will be explained.

After reading through the contents of the respondent information sheet, all participants who willingly show consent to be part of the study will be given a consent form to sign. Afterward, they will be requested to fill out a structured pre-tested baseline breast cancer knowledge, beliefs, and practice questionnaire in the English language. 1 month and 3 months post intervention, the same questionnaire will be administered to the intervention group and the control group respectively.

The same strategy will be followed in the control colleges, teachers will be selected randomly, but the purpose and procedure about the intervention will not be discussed, only the data collection procedure will be discussed with them. After getting written consent from them, they will be requested to fill in the questionnaire at the baseline, 1-month post-intervention (intervention delivered to intervention group), and three months post-intervention.

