### 2.5.2 Sampling Frame

A comprehensive list of government colleges in Hyderabad district.

A complete list of teachers employed in government colleges in Hyderabad district, including their names and employment ID numbers obtained from the relevant department.

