**Step 2:**

**Randomize Within Blocks:**

- Each block will be randomly assigned to one of the treatment groups. For example, flip a coin or use a random number generator to determine whether Block 1 goes to the intervention or control group, and similarly for Block 2.

**Required sample size:** The Total sample size required for the second phase of study is 114, that is 57 participants in each arm.

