**Step 4: Proportionate Stratified sampling:**

Proportionate stratified sampling from all colleges based on faculty will be performed once the assignment of colleges is done to the intervention and control group, e.g., 2 colleges in the intervention group.

To calculate the proportions for each faculty within the intervention group (57) for the two colleges (A & B), these steps can be followed.

Proportions will be calculated based on the number of teachers in each faculty at each college.

e.g.

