**Step 5 Random sampling:**

Participants will be selected randomly by random number generators, randomly selected participants will be invited for the study, exclusion and inclusion criteria will be discussed; written consent will be obtained from eligible participants, and baseline data will be collected.

[figure not shown]

Figure III. CONSORT flow diagram of the study—adapted from Campbell (Campbell, Elbourne, & Altman, 2004)

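### Briefing, consent and baseline come after the college's arm is known, with a different spoken briefing in control colleges, which risks recruitment bias of unknown size and direction

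*Combined protocol and SAP*

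**What the plan says.** The order is set in section 2.7. Step 1 forms two blocks of two colleges. In Step 2, "Each block will be randomly assigned to one of the treatment groups". Step 3 sets the number of teachers per college. Step 4, the stratified sampling of teachers, "will be performed once the assignment of colleges is done to the intervention and control group". In Step 5, "randomly selected participants will be invited for the study, exclusion and inclusion criteria will be discussed; written consent will be obtained from eligible participants". The baseline questionnaire comes after that.

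Section 2.11 describes what teachers are told before they consent. The general rule is: "All the selected participants will be informed about the purpose and procedures of breast cancer awareness and BSE practices educational intervention trial". Control colleges follow the same approach with one exception: "but the purpose and procedure about the intervention will not be discussed, only the data collection procedure will be discussed with them". Control teachers sign consent and complete the baseline questionnaire after that restricted briefing.

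Two features protect the draw. The sampling frame in 2.5.2 is "A complete list of teachers employed in government colleges in Hyderabad district", and in Step 5, "Participants will be selected randomly by random number generators".

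**The concern.** In a cluster trial, randomising colleges balances the arms in expectation only for the teachers who would be recruited whichever arm their college received. If teachers are approached after allocation, and the approach itself depends on the arm, those who agree may differ between arms before the intervention has done anything. Unwilling teachers are excluded (2.5.1, exclusion criteria for teachers), so consent is a filter, and it works under different information in each arm.

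The outcomes make this matter. Regular breast self-examination (BSE) is self-reported, as are knowledge and beliefs. An offer of BSE training may attract or deter teachers according to how much they already practise, or how ready they are to start. Teachers who have just heard the trial's purpose may also answer the baseline questionnaire differently from those told only about data collection. A larger sample cures neither problem, and recruitment cannot be redone afterwards.

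**Working it through.** **1. Order of steps.** Reading section 2.7 with 2.11 gives: form blocks, assign blocks to arms, set quotas, sample teachers, brief, consent, baseline. Every contact with a teacher comes after allocation.

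**2. Safeguards.** The text states no recruiter who is unaware of the arm, no count of refusals by college, and no rule for replacing refusers. Because 2.11 makes the briefing depend on the arm, whoever gives it must know the arm. The design is called single blind, but who is blinded is not said.

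**3. Where bias can and cannot enter.** The draw is random from a complete list, so drawing it after allocation does little harm in itself. Bias can enter at the briefing, at consent and in the baseline answers.

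**4. Size.** No figure in the plan measures this, and the sample size of 114 does not change. The only usable input is the 26% control prevalence of regular practice in Appendix II (P2). The rest is assumed: no true effect, consent unrelated to practice in control colleges, and in intervention colleges consent of 90% among regular practisers and *c* among the others. Prevalence among intervention recruits is then 0.26 × 0.9 / (0.26 × 0.9 + 0.74 × *c*).

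| *c* | Calculation | Prevalence | Difference from 26% |
| --- | --- | --- | --- |
| 90% | 0.234 / 0.900 | 26.0% | 0 points |
| 80% | 0.234 / 0.826 | 28.3% | 2.3 points |
| 70% | 0.234 / 0.752 | 31.1% | 5.1 points |
| 60% | 0.234 / 0.678 | 34.5% | 8.5 points |
| 45% | 0.234 / 0.567 | 41.3% | 15.3 points |

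With a base prevalence of 10% to 40%, the four unequal patterns give 1.1 to 17.1 points. If instead the offer attracts non-practisers (60% consent among practisers, 90% among others), prevalence is 0.156 / (0.156 + 0.666) = 19.0%, a difference of −7.0 points.

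**5. What the planned analysis does with this.** The analysis section plans generalized estimating equations with group, time and group-by-time, and also lists plain between-arm tests (chi-square, Fisher, t, Mann-Whitney).

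- *Stable difference in practice.* The odds ratio between arms from selection is the ratio of consent rates, for example 0.9/0.6 = 1.5. If practice does not change, it is 1.5 at baseline and 1.5 at follow-up, and the interaction is 1.5/1.5 = 1. The group-by-time term removes it. A plain test at follow-up carries it in full.
- *Difference in readiness to change.* Suppose the share of ready teachers differs between arms by d, and ready teachers would raise their practice by g more than others without any programme. On the percentage scale the spurious difference in change is d × g. If d spans the same 1.1 to 17.1 points and g lies between 0 and 1, this runs from 0 to 17.1 points. Neither the interaction term nor the plain tests remove it, and no baseline covariates are named.
- *Baseline shifted by the briefing.* If hearing the purpose raises reported baseline practice in the intervention arm by b points, the estimated change falls by b. This works against the intervention. A comparison at follow-up alone avoids it only because it ignores baseline.

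**The case against.** The strongest reply is that the plan already limits the damage. Selection is random from a full list, baseline is measured in both arms, and group-by-time takes out any stable baseline difference. The planned effect is 85.6% − 26% = 59.6 points, far above any figure in the table. Sampling error is also sizeable: with 26% in both arms and 57 per arm, ignoring clustering, the standard error is √(2 × 0.26 × 0.74 / 57) = 8.2 points. Withholding the purpose from control teachers may also be deliberate, to avoid prompting BSE or to support the single blind.

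Much of this stands. The random draw and the interaction term do what is claimed for them. But the interaction does not reach readiness to change, and its reference point is itself taken after the arm-specific briefing. The comparison with 59.6 points reassures only if the true effect is near that size, and it says nothing about the knowledge and belief scores. Prompting is a fair worry, but control teachers complete a questionnaire about BSE in any case.

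A reader might infer more than the documents support:

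- That sampling after allocation is itself biased. Random selection from a complete list answers this.
- That the bias must favour the intervention. The table's sign reverses under an equally plausible pattern, and a shifted baseline works the other way.
- That control teachers also receive a different written sheet. The contents list shows one information sheet in Appendix III, whose text I could not see. Only the spoken briefing is shown to differ.
- That having two colleges per arm is what makes the bias inseparable from the effect. Differential consent would be the same problem with many colleges; few clusters is a separate matter.

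**Conclusion.** The point holds as a risk. Teachers are briefed, consented and surveyed at baseline after their college's arm is assigned, and 2.11 prescribes a different spoken briefing before consent in control colleges. This exposes the comparison to recruitment bias and puts the two baselines on different footings.

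The size and direction are unknown. The figures above rest entirely on assumed consent rates and show only what moderate to strong selection could do; they are not estimates for this trial. A stable difference in practice would be handled by the group-by-time term. A difference in readiness to change, or a baseline moved by the briefing, would not. Since the weakness cannot be repaired after recruitment and is cheap to prevent, the plan should be changed before teachers are approached.

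**What to change.** Reorder section 2.7 and align 2.11 with it:

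1. Form the two blocks and draw the teacher sample in all four colleges. The quotas allow this: each block supplies 57 whichever arm it receives (31 + 26 and 34 + 23).
2. Give one neutral briefing and one information sheet everywhere: a women's health education study, with the programme delivered either now or after the 3-month follow-up. This is truthful for both arms, because 2.12 already gives controls the programme after the last follow-up.
3. Obtain consent and complete the baseline questionnaire in all four colleges.
4. Only then randomise the blocks to arms.
5. Delete the control-only briefing exception in 2.11, and the condition in Step 4 that sampling waits for assignment.

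If this order is impossible, use a recruiter who does not know the arm, give identical information, and prespecify adjustment for baseline practice. In either case report, by college, the numbers approached, eligible, refusing and consenting.

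The cost is a reordering of the protocol, one common sheet for the ethics committee to accept, and a slightly later draw. The real downside is that control teachers learn that a programme will come later, which may prompt some BSE during follow-up and dilute the contrast. Neutral wording limits this.

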## 2.12 Delivery of intervention module and participation

1. **Knowledge-based awareness session.**

After the collection of baseline data, a 60-minute one-day session of the educational program on breast cancer awareness and screening will be delivered to each intervention college by the study researcher with a group of 20 to 25 participants. Before implementing the intervention, researchers will ensure that all the participants must have a mobile phone to receive the reminder SMS and to watch the BSE video clip. The procedure description will be as follows,

One hour presentation along with a short video of 5 minutes duration about BSE performance will be presented, which will consist of general structure as well as functioning of normal breast, awareness on breast health, basic knowledge on breast cancer, and education on various screening methods will be provided by the researcher.

1. **Skill based training session.**

Followed by the training session, in which a breast model made up of silicon having multiple lumps on it will be used for demonstration of BSE method, during this section, participants will learn the palpation technique, the search strategy, and signs of BC that are important for respondents to know. Later, the participants will be asked to perform BSE on the model and look for abnormalities.

1. **Take home messages for participants.**

A leaflet with the same information that was provided in the session will be given to every participant when the educational session ends.

A short film about BSE performance will be sent to the participants via WhatsApp, and a BC logo wall hanging will also be provided to be hung in the participants ‘room. Such materials will be believed to remind participants about BCS practice and monthly BSE performance. A short WhatsApp reminder message will be sent to all participants of the intervention group for the period of three months.

1. **Souvenirs as a reminder for breast self-examination**

Some souvenirs will be given to the participants, like a key chain, a writing pen, and a note pad with the breast cancer logo and a message “**know your risk**” get screening timely! To remind them of breast self-examination.

